**Figure 1 figure1:**
[figure not shown]
Overview of study design with primary and secondary outcomes. CBT/MM: cognitive behavior therapy/mindfulness and meditation.

**Table 1 table1:** Study timeline from weeks 1-20.

Time point		Screening	Week 1	Week 2	Week 7	Week 12	Week 16	Week 20
		Visit 1	Visit 2	Visit 3	Visit 4	Visit 5	Visit 6	Visit 7
**Enrollment**								
	Eligibility screen	✓						
	Informed consent	✓						
	MINI^a^	✓						
	Randomization		✓					
**Interventions**								
	Ketamine-hydrochloride infusion (arm 1 and arm 3)			✓	✓	✓		
	Remote CBT/MM^b^ (arm 2 and arm 3)		✓	✓	✓	✓	✓	
	In-person CBT/MM (arm 2 and arm 3)			✓	✓	✓		
**Assessments**								
	Baseline data		✓					
	Semistructured interviews		✓^c,d^	✓^d^	✓^d^	✓^d^		✓^c,d^
	Pregnancy test (if applicable)^e^			✓	✓	✓		
	Questionnaires: PROMIS-PI^f^, PGIC^g^, GAD-7^h^, PHQ-9^i^, and PCS^j^		✓	✓	✓	✓	✓	✓
	Adverse events			✓	✓	✓	✓	✓

^a^MINI: Mini International Neuropsychiatric Interview.

^b^CBT/MM: cognitive behavior therapy/mindfulness and meditation.

^c^Participants randomized to receive CBT/MM alone (arm 2), will receive a semistructured interview on weeks 1 and 20.

^d^Participants randomized to receive ketamine-hydrochloride infusion + CBT/MM (arm 3) will receive a semistructured interview on weeks 1 and 20 as well as a semistructured interview during the ketamine infusion on weeks 2, 7, and 12.

^e^Only female participants randomized to receive ketamine-hydrochloride alone (arm 1) or the ketamine-hydrochloride infusion + CBT/MM (arm 3) will require a pregnancy test on the day of infusion.

^f^PROMIS-PI: Patient-Reported Outcomes Measurement Information System.

^g^PGIC: Patient Global Impression of Change Scale.

^h^GAD-7: Generalized Anxiety Disorder-7.

^i^PHQ-9: Patient Health Questionnaire-9.

^j^PCS: Pain Catastrophizing Scale.

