#### Blinding Mechanism

The intervention delivery providers (anesthesiologists and psychologists) and other members of the research team will be aware of each participant’s assigned intervention. Within the research team, blinded members will be responsible for inputting all of the data into the REDCap (Research Electronic Data Capture; Vanderbilt University) database, with the exception of any ketamine-specific data, that is, semistructured interviews after the ketamine intervention and any adverse events. Following data collection, we will request blinded staff to record their “best guess” of each patient’s intervention to assess blinding efficacy. The research team currently has 1 blinded member who will serve as the outcome assessor and be responsible for data input.

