#### Secondary Outcome

The secondary outcomes chosen for the definitive trial follow consensus recommendations of core domains that should be addressed in studies examining chronic pain. Information will be collected in these domains as part of the pilot trial using survey-based outcome assessments, either in person during study visits or over the telephone by trained research personnel. The following pain score questionnaires will be used:

Pain intensity on an 11-point (0-10) Numeric Rating Scale.Pain interference on the Patient-Reported Outcomes Measurement Information System (PROMIS-PI) scale.Catastrophic thinking about pain, as measured by the Pain Catastrophizing Scale (PCS).Features of depression, as measured by the Patient Health Questionnaire-9 (PHQ-9).Features of anxiety, as measured by the Generalized Anxiety Disorder-7 (GAD-7).Patient Global Impression of Change Scale (PGIC).

Secondary clinical outcomes will include changes relative to baseline assessment in pain intensity and pain interference at week 20 (4 weeks post-completion of treatment; Figure 1). Scores for all outcomes at weeks 2, 7, 12, 16, and 20 will be compared to baseline scores to assess any progressive additive effects between the treatments. For any patients who withdraw before week 20, their last documented responses will be used as a comparison against baseline data. Patients will be allowed to adjust the dosages of other analgesic medications in conjunction with their primary physician. Analgesic medication use and doses will be tracked at the above time points to assess changes over time. Semistructured interviews will be conducted at 2 points within the study period: at weeks 1 and 20 and after the ketamine infusions (Table 1). The interviews will be audio-recorded to ensure the responses are accurately captured. In-person interviews will be recorded with an encrypted device, and phone interviews will be recorded through the Unity Health Zoom (Zoom Video Communications Inc) recording option. The audio recording files will be saved on St. Michael’s Hospital secure and restricted servers, and the files will be labeled by the study number. The recordings will be transcribed by the research team, and after verifying that the transcriptions are accurate, the audio recordings will be destroyed. Questionnaires will be delivered to patients at prespecified time points, as outlined in the study timeline below.

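### By Table 1, the week-1 and week-20 interviews go only to the two CBT/MM arms, so assessment contact differs by arm at baseline and at the week-20 secondary clinical endpoint

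*Protocol article*

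**What the plan says.** Table 1 of the protocol article ticks semistructured interviews at weeks 1, 2, 7, 12 and 20. The ticks at weeks 1 and 20 carry footnotes c and d; those at weeks 2, 7 and 12 carry d alone.

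- Footnote c: "Participants randomized to receive CBT/MM alone (arm 2), will receive a semistructured interview on weeks 1 and 20".
- Footnote d gives Arm 3 those same two interviews and adds three more: "as well as a semistructured interview during the ketamine infusion on weeks 2, 7, and 12".

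The same table ticks the questionnaires at weeks 1, 2, 7, 12, 16 and 20. The Follow-Up Data section confirms that they apply in all arms, and the Arm 1 section says that patients are not blinded.

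Two other places describe the interviews differently. The Secondary Outcome section says "Semistructured interviews will be conducted at 2 points within the study period: at weeks 1 and 20 and after the ketamine infusions (Table 1", naming no arms but pointing to the table. The Blinding Mechanism section has blinded members enter all data except ketamine-specific data, which it explains as "semistructured interviews after the ketamine intervention and any adverse events".

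The clinical endpoint is set in the Secondary Outcome section: "changes relative to baseline assessment in pain intensity and pain interference at week 20".

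**The concern.** Pain, interference, mood and global change are all rated by patients who know their treatment. If one arm has a structured conversation with study staff at the visit where those ratings are made and another arm does not, the measurement procedure itself differs by arm. Any effect of that conversation on the ratings would be mixed with the treatment effect, and no later analysis could separate the two. The comparisons exposed at week 20 are Arm 3 versus Arm 1 and Arm 2 versus Arm 1. The first is one of the two comparisons that the secondary objective asks for.

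Blinding is the second matter. One blinded person serves as both outcome assessor and data-entry member. If interviews at weeks 1 and 20 exist only for Arms 2 and 3 and pass through that person's hands, their mere existence narrows the allocation.

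**Working it through.** No design figure is involved, so the check is a count from Table 1 and a comparison of the three places.

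**Step 1. Interviews per participant under footnotes c and d**

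| Week | Arm 1 | Arm 2 | Arm 3 | Questionnaires, all arms |
|---|---|---|---|---|
| 1 (baseline) | 0 | 1 | 1 | yes |
| 2 | 0 | 0 | 1 | yes |
| 7 | 0 | 0 | 1 | yes |
| 12 | 0 | 0 | 1 | yes |
| 16 | 0 | 0 | 0 | yes |
| 20 (endpoint) | 0 | 1 | 1 | yes |
| Total | 0 | 2 | 5 | |

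At weeks 1 and 20 the difference in interviews is 1 − 0 = 1 for Arm 3 versus Arm 1, 1 − 0 = 1 for Arm 2 versus Arm 1, and 1 − 1 = 0 for Arm 3 versus Arm 2. At weeks 2, 7 and 12 only Arm 3 is interviewed.

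**Step 2. The other reading.** If the Secondary Outcome sentence applies to every arm, Arm 1 would have up to 2 + 3 = 5 interviews (weeks 1 and 20 plus three infusions), Arm 2 would have 2 and Arm 3 would have 5. The imbalance at weeks 1 and 20 then disappears.

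**Step 3. Which reading is better supported.** The Secondary Outcome sentence defers to Table 1. Within that table, footnote e (pregnancy tests) names Arm 1 and Arm 3 together where both are meant, so leaving Arm 1 out of c and d looks deliberate. Against this, the Blinding Mechanism wording ties interviews to receipt of ketamine, which Arm 1 also receives. The table reading is the stronger one, but the article does not settle the matter. It also differs on timing: footnote d places the infusion-visit interview during the infusion, while the two text sections place it afterwards.

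**Step 4. Direction.** The endpoint is a change, week 20 minus baseline. Under Table 1, Arms 2 and 3 are interviewed at both ends and Arm 1 at neither. If an interview shifts a rating by a at week 1 and by b at week 20, the change score in Arms 2 and 3 shifts by b − a, and in Arm 1 by 0. The document gives neither a nor b, nor the sign of either. The two need not be equal, because the week-1 interview precedes the first infusion and the week-20 interview follows the end of treatment. So b − a may be positive, negative or zero.

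**Step 5. Blinded data entry.** The exception covers interviews after ketamine and adverse events. Arm 2's interviews at weeks 1 and 20 follow no ketamine, and the week-1 interview in Arm 3 comes before any infusion. The wording does not expressly cover Arm 3's week-20 interview, which is not held at an infusion visit. Under Table 1, a record of any of these excludes Arm 1.

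**The case against.** The strongest reply is that bias needs the interview to come first. The order of instruments within a visit is operational detail that an article may leave to the full protocol, and the interview content is not given either. Interviews and questionnaires may even be separate contacts, since telephone is allowed for both. This stands: priming is a possibility and not a documented event, and the unstated order is not itself a fault. What remains is what the article does state, namely an arm-specific interview schedule and a data-entry exception that covers only part of it.

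A reader might infer that the bias would favour the combined arm, as hypothesised. The documents do not support that. The same imbalance exists at baseline, talking about pain could raise ratings as easily as lower them, and Arms 2 and 3 are treated alike at week 20. Nor can a size be given, since the article states no target effect or standard deviation.

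Two further replies limit the weight of the point. First, Arms 2 and 3 already receive about 16 hours of counselling that Arm 1 does not, and the Discussion acknowledges that patients are unblinded, so one or two interviews add little to that contact. The counselling is part of the treatment being compared, however, and an interview at the assessment visit is not. Second, the comparison is imprecise. Assuming equal allocation of the 30 participants (10 per arm), the standard error of a two-arm difference is √(1/10 + 1/10) ≈ 0.45 standard deviations. A modest shift would be hidden in that noise. This lowers the stakes but does not justify keeping an avoidable difference.

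**Conclusion.** The point holds in limited form. On the reading of Table 1 that its footnotes best support, assessment contact differs by arm at baseline and at the week-20 secondary endpoint (0 interviews in Arm 1, 1 each in Arms 2 and 3, at each of those visits). This could bias comparisons with Arm 1 if interviews come first. Its direction and size are unknown. Arm 3 versus Arm 2 is not affected by unequal interviewing at week 20, though it is exposed at weeks 2, 7 and 12. Separately, the data-entry exception is too narrow to keep interview records at weeks 1 and 20 from revealing that a patient is not in Arm 1.

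Both conclusions assume that Table 1 governs. If all arms are interviewed at weeks 1 and 20, the imbalance and the clue at those visits disappear, and the remaining problem is that Table 1 is wrong. The consequence is small, because feasibility is the primary outcome and the article says that efficacy is not powered. It matters mainly because the pilot is meant to inform the sample size of the definitive trial.

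**What to change.** 1. Reconcile the Secondary Outcome section, the Blinding Mechanism section and Table 1 on which arms are interviewed, at which weeks, and whether the infusion-visit interview is held during or after the infusion.
2. State that at every visit with both, above all weeks 1 and 20, all questionnaires are completed before any interview.
3. Have unblinded staff already on the team conduct and enter all semistructured interviews, not only those after ketamine, so that the blinded assessor never sees whether one took place.

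The cost is a few lines in the visit schedule and the blinding section, with no added visits, patients or staff. The article reports that enrolment had not begun as of November 1, 2023. If it has still not begun, the change can apply to every participant.

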### Ethical Considerations

This study will be conducted in accordance with the ethical principles laid down in the Declaration of Helsinki, the protocol, Good Clinical Practice guidelines, and applicable regulatory requirements. This study received a “No Objection Letter” from Health Canada on October 13, 2022, indicating the study protocol was deemed acceptable.

Full written informed consent will be obtained from participants before conducting any study activities. The study was reviewed and approved by the Research Ethics Board at St. Michael’s Hospital on May 5, 2023 (22-217). This trial was designed and will be reported according to the CONSORT (Consolidated Standards of Reporting Trials) clinical trials statement checklist and the CONSORT-Outcomes 2022 extension [16].

## Results

### Prestudy Screening

Eligible participants will be screened at the Chronic Pain Clinic at St. Michael’s Hospital. Participants diagnosed with chronic neuropathic pain that meet the criteria from the ID pain questionnaire will be approached and asked to consider study participation.

After participants have provided informed consent, they will be asked about their medical comorbidities, psychiatric history as based on the Mini International Neuropsychiatric Interview, history of ketamine hypersensitivity, and concomitant medications to confirm eligibility. If a participant is eligible to participate in the study, the participant will be enrolled in the study, and the study coordinator will book an appointment for the participant’s study intervention.

At this current point, November 1, 2023, the study has not started enrolling and consenting patients.

### Baseline Data

After initial screening and informed consent are obtained, the following data will be collected at baseline (week 1):

Demographic information: age, sex, gender, height, and weight.Detailed data regarding current medications and medical comorbidities, as well as medication history, is collected by our standard intake form.Chronic neuropathic pain severity and other relevant covariates will be assessed at baseline using:PROMIS-PIPCSPHQ-9GAD-7PGIC

### Follow-Up Data

In all arms, at each follow-up visit, participants will complete the PROMIS-PI scale, PCS, PHQ-9, GAD-7, and the PGIC to assess outcome measurements. Follow-ups will be conducted every 4 weeks over the phone to maintain the blindness of the research team.

For females, a urine pregnancy test will be required for those randomized to the ketamine-hydrochloride infusion alone or the ketamine-hydrochloride infusion+CBT/MM arms in order to confirm that the patient is not pregnant before each ketamine infusion treatment.

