### Outcome Measures

#### Primary Outcome

The primary outcome of this pilot trial is to determine the feasibility of a large-scale multicenter trial. Feasibility outcomes will include the following variables, with all thresholds listed in parentheses:

Recruitment success (with the specific aim of recruiting all necessary patients within the first year of the trial period).Adequate consent rate (>30% of eligible patients consent to participate in the study).Percentage of patients who complete all medication and psychotherapy visits (ie, intervention adherence; >90%).Percentage of patients who withdraw from the study (eg, due to side effects or other reasons; <20%).Percentage of patients with incomplete pain intensity and pain interference data at 1 month and stated or ascribed reason (eg, withdrawal due to side effects, loss of follow-up, or missing data; <10%).Rate of adverse outcomes (ie, 0 serious adverse events).

Based on the result for each primary feasibility outcome, we will determine whether the definitive study is feasible as proposed (ie, all feasibility targets are met), feasible with protocol modifications (modifications specified), or not feasible because feasibility targets could not be met even with protocol modifications. These cutoffs, identified in the parentheses above, will help determine whether protocol changes are required before proceeding with a definitive trial.

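### Pain intensity (0-10 NRS) is a named outcome but is missing from the baseline list, the follow-up list and Table 1, while the PGIC, a rating of change, is given a baseline

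*Protocol article*

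**What the plan says.** All references are to the protocol article.

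- **Outcome definition (Secondary Outcome).** Six instruments are to be used. The first is "Pain intensity on an 11-point (0-10) Numeric Rating Scale"; the others are PROMIS-PI, PCS, PHQ-9, GAD-7 and PGIC.
- **Planned comparisons (same section).** "Secondary clinical outcomes will include changes relative to baseline assessment in pain intensity and pain interference at week 20". In addition, "Scores for all outcomes at weeks 2, 7, 12, 16, and 20 will be compared to baseline scores". The section then points to the study timeline, Table 1, for when questionnaires are given.
- **Table 1, Assessments.** The questionnaire row reads "Questionnaires: PROMIS-PI^f^, PGIC^g^, GAD-7^h^, PHQ-9^i^, and PCS^j" and is ticked at weeks 1, 2, 7, 12, 16 and 20. No row names the NRS.
- **Baseline Data.** "Chronic neuropathic pain severity and other relevant covariates will be assessed at baseline using" is followed by PROMIS-PI, PCS, PHQ-9, GAD-7 and PGIC.
- **Follow-Up Data.** "In all arms, at each follow-up visit, participants will complete the PROMIS-PI scale, PCS, PHQ-9, GAD-7, and the PGIC to assess outcome measurements".
- **Primary Outcome.** One feasibility criterion, with a limit of under 10%, is "Percentage of patients with incomplete pain intensity and pain interference data at 1 month".
- **Inclusion criteria (Textbox 1).** The NRS appears once more, as an average score above 3 over the week before inclusion.

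**The concern.** The section that defines the outcomes and the three places that say what is collected disagree about the same scale. Visit procedures and data capture forms are normally built from the schedule, and a pain score that was not asked for at a visit cannot be recovered later.

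Three things depend on the NRS:

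- **The secondary aim and the clinical hypothesis.** Both name pain intensity alongside pain interference.
- **A primary feasibility criterion.** Completeness of pain intensity data is part of it, and Outcome Analysis classifies the trial by whether all feasibility outcomes are met. A scheduling gap could therefore affect the feasibility conclusion.
- **Planning of the definitive trial.** The Discussion says the pilot will inform its sample size. Without NRS data there is no estimate of variability or change for pain intensity.

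The PGIC raises a smaller and separate problem. It asks how much the patient has changed. At week 1 there is no change since the start of study treatment to rate, so that score gives no meaningful reference for later ratings.

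**Working it through.** No power calculation or other stated figure bears on this point. The check is a side-by-side reading of the lists, followed by a count.

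**Step 1. Which list names which instrument**

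| Instrument | Secondary Outcome | Baseline Data | Follow-Up Data | Table 1 row |
|---|---|---|---|---|
| NRS | yes | no | no | no |
| PROMIS-PI | yes | yes | yes | yes |
| PCS | yes | yes | yes | yes |
| PHQ-9 | yes | yes | yes | yes |
| GAD-7 | yes | yes | yes | yes |
| PGIC | yes | yes | yes | yes |

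Six instruments are defined and the same five are scheduled in all three places. The NRS is the only one missing.

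**Step 2. Scheduled occasions.** Table 1 ticks the questionnaire row at six time points: week 1 as baseline, then weeks 2, 7, 12, 16 and 20.

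- NRS: 0 of 6.
- PROMIS-PI: 6 of 6, so baseline and week 20 are both covered.
- PGIC: 6 of 6, including week 1.

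**Step 3. The two named week-20 change analyses.**

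- Pain interference is week-20 PROMIS-PI against week-1 PROMIS-PI. Both are scheduled, so the analysis can be done as written.
- Pain intensity is week-20 NRS against baseline NRS. Neither value is scheduled.

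**Step 4. Can the eligibility NRS stand in?** It is not designated as the baseline; Baseline Data places baseline at week 1 with its own list. Even if it were adopted, it supplies no value at week 2, 7, 12, 16 or 20, so the change still has only one end.

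**Step 5. The completeness criterion.** It covers pain intensity and pain interference at 1 month. Whichever visit is meant by 1 month, the NRS is not listed there. If the lists were followed to the letter, all 30 of 30 participants would lack pain intensity data (30/30 = 100%) against a limit of under 10%. This figure describes the literal schedule and is not a forecast.

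**Step 6. PGIC.** It is in the baseline list, is ticked at week 1, and is one of the outcomes covered by the sentence that compares all scores with baseline. Its five follow-up ratings (weeks 2, 7, 12, 16 and 20) are scheduled and can be used on their own.

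**The case against.** The strongest reply is that the article contradicts itself but does not drop the measure. Secondary Outcome is as operative as the lists: it says the NRS will be used, and its sentence on all outcomes gives the scale explicit time points. The feasibility criterion presupposes that pain intensity is collected, and the Baseline Data lead-in speaks of pain severity. The NRS was plainly intended.

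That stands as far as intent goes. It limits what can be claimed, but it does not remove the conflict, because the same section sends the reader to Table 1 for timing and Table 1 omits the scale. Nor is this an article leaving detail to a fuller document: it lists the instruments in three places and omits the same one each time.

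Three stronger readings are tempting, and the document does not support them:

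- **That neither week-20 change analysis can be done.** PROMIS-PI is fully scheduled, so only pain intensity is affected.
- **That pain intensity data are certain to be lost in every participant.** This follows only if the lists override Secondary Outcome.
- **That the PGIC analysis subtracts a meaningless week-1 value.** The text says scores are compared with baseline and that secondary outcomes are modelled as continuous measures; it does not say that PGIC values are subtracted. The fault is an unneeded week-1 form and an overly broad sentence.

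It is also fair to say that these clinical outcomes are secondary and that the article describes the trial as not powered for them. That lowers the stakes for the efficacy comparison, but not for the feasibility criterion, which is primary.

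**Conclusion.** The point holds as an internal inconsistency that should be resolved before recruitment. The NRS is a defined outcome with planned comparisons at week 20 and at five follow-up time points, but it is scheduled on none of the six occasions. On a literal reading of the schedule, one of the two named week-20 change analyses and the pain intensity half of one primary feasibility criterion have no scheduled data. The pain interference analysis is sound on this point.

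The consequence rests on one assumption: that visit procedures and forms are built from Table 1 and the two lists. If they are built from Secondary Outcome instead, the NRS would be collected and the remedy is purely editorial.

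The PGIC point is minor. Its follow-up ratings are usable; its week-1 rating and its place in the baseline comparison are not well defined.

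**What to change.** - Add the 0-10 NRS to the lists in Baseline Data and Follow-Up Data and to the Table 1 questionnaire row at weeks 1, 2, 7, 12, 16 and 20.
- State the recall period of the outcome NRS. The entry criterion uses a 7-day average; the outcome definition gives none.
- Remove the PGIC from week 1 in Table 1 and from the baseline list.
- Exempt the PGIC from the sentence that compares all outcomes with baseline, and compare its follow-up ratings between arms.

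Designating the screening NRS as baseline would settle the baseline end only; the follow-up measurements would still have to be scheduled.

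The cost is one single-item scale per visit, one questionnaire fewer at week 1, and edits to two lists, one table and the data capture form. The article reports that recruitment had not started as of November 1, 2023, so if the change is made before the first participant is enrolled, no collected data are affected.
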